### Design

This study comprised a stepped wedge, cluster randomised controlled trial that was conducted in two phases on the basis of student population (Study 1 = secondary school age participants; Study 2 = primary school age participants). Stepped wedge designs are similar to cross-over trials, however only involve uni-directional cross-over resulting in all participants receiving the intervention by the conclusion of the trial. The waiting list for the “Girls on the Go!” program was used to generate the control period. The intervention program was designed to be delivered to a group of participants from the same school at the same time, thus randomising students in clusters (school) was seen as an appropriate unit of randomisation.

A total of 12 schools that requested the program were separated into Study 1 or 2. Within each study, schools were matched on the basis of number of students (into triplets for Study 1 and pairs for Study 2) and then randomly allocated (computer generated sequence developed by investigator blinded to school identity) to receiving the intervention immediately or having a waiting list period. Study 1 had one waiting list period of one school term, creating two steps in the stepped-wedge design (i.e. 3 schools were provided with “Girls on the Go!” each term over 2 terms–see Figure 1). Study 2 had two waiting list periods of one and two school terms, creating three steps in the stepped-wedge design (i.e. 2 schools were provided with “Girls on the Go!” each term over 3 terms–see Figure 2).

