### Pilot of the “Girls on the Go!” intervention

A retrospective program review of the data collected from participants between 2001 and 2009 was conducted. Ethical approval was received by the Southern Health’s Research Directorate (Research Project number: 09252Q, HREC09252). Questions examining self-esteem, self-efficacy (responses captured using 5 point visual analogue scale), and satisfaction with body image (responses captured using 4 point visual analogue scale) were compared between pre and post program assessments using ordered logit regression analysis with clustering by participant to account for dependency between pre and post assessments within participant.

Ordered logit regression calculates the increase or decrease in odds of moving up one level in the ordinal dependent variable associated with a one unit change in the independent variable. The location of the interquartile range for each of these items was located higher in the scale range in the post program assessment compared to the pre-program assessment indicating that the program was beneficial to these outcomes. The odds (95% CI), p-value of moving up one level for self-esteem with completing the program was 4.89 (3.47, 6.88), p < 0.001, for self-efficacy was 4.65 (3.42, 6.32), p < 0.001, and for satisfaction with body image was 3.68 (2.66, 5.11), p < 0.001. Despite these promising results, the limitations of the pre-post intervention research design dictated that further work using randomised trial methodology was necessary to establish the efficacy of the “Girls on the Go!” program.

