### Analyses

The effect of being exposed to the “Girls on the Go!” program will be examined using a linear mixed model analysis approach, suitable for analysing longitudinal data where there is likelihood of missing data or loss to follow-up. The model that will be constructed to conduct this analysis will require construction of an independent variable, labelled “Girls on the Go”. This variable will be coded a 0 for observations where the group had not yet been exposed to the “Girls on the Go!” intervention (e.g. In study 1; at baseline for all schools and also at the first follow-up assessment but only for schools in the “Waiting List” period–see Figure 1), and 1 for observations where the participants had already received the “Girls on the Go!” intervention (e.g. In study 1; at the first follow-up assessment for schools in the first “Girls on the Go” period and also for all schools at the second follow-up assessment). Raw summative outcome measurement scores will be used as the dependent variables.

The mixed model analysis will involve investigating the effect of the “Girls on the Go” variable on the dependent variable, adjusting for assessment number (to account for the effect of time). The “Girls on the Go” variable will be entered into the model as a fixed factor, while assessment, student and school will be entered as random factors. Assessment will be nested within student which will be nested within school which will create a 3-level model that takes into account the longitudinal, clustered nature of data collected in this study. Maximum likelihood methods of estimation will be employed to address issues of missing data under the assumption of Missing At Random.

To investigate whether the effect of the “Girls on the Go!” program was sustained, a “Girls on the Go” by assessment interaction effect will be added to the same analysis models. A significant interaction effect in these models will indicate whether any changes brought about at the initial post-“Girls on the Go!” follow-up assessment were sustained. We will also examine the data from the group that received the “Girls on the Go!” program first and compare student results between the first and subsequent post-intervention follow-up assessments in isolation using linear regression clustering data by individual student.

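### The supplementary check of a sustained effect follows the first-start schools alone, so it cannot separate fading from ordinary term-to-term change

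*Protocol article*

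**What the plan says.** The Analyses section sets out two checks of a sustained effect. In the first, a programme "by assessment interaction effect will be added to the same analysis models". The second starts "We will also examine the data from the group that received the" programme first, and will "compare student results between the first and subsequent post-intervention follow-up assessments in isolation using linear regression clustering data by individual student".

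The main model, by contrast, uses all schools, "adjusting for assessment number (to account for the effect of time". Its coding shows when the other schools are observed. In Study 1 the variable is 0 "at baseline for all schools and also at the first follow-up assessment but only for schools in the" waiting-list period, and it is 1 for first-start schools at follow-up 1 and "also for all schools at the second follow-up assessment".

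Under Design, start order is randomised. Study 1 has two sequences of 3 schools. For Study 2, "Study 2 had two waiting list periods of one and two school terms, creating three steps in the stepped-wedge design", with 2 schools per step. Under Procedure, Study 2 collects data in the same way with one more follow-up.

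**The concern.** The second check compares a treated group with itself over later terms. Girls mature, and terms differ. If scores drift downward for everyone, the check shows fading that did not occur. If they drift upward, it hides fading that did.

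The article accepts that time matters, since it adjusts the main model for it. Of its own pilot it says that "the limitations of the pre-post intervention research design dictated that further work using randomised trial methodology was necessary". The later-start schools are randomised and assessed at the same points, so a controlled comparison is available without new data.

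What is at stake is the durability conclusion. The Background notes that some similar programmes showed no sustained benefit, so readers will look for this result.

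**Working it through.** The article states no figure for this check, so there is none to reproduce. The question is what each comparison estimates.

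**Layout** (from the text of Design, Procedure and Analyses). Let t1, t2, t3 be the change common to all schools since baseline at each follow-up. Let d0, d1, d2 be the programme effect just after the programme, one term later and two terms later. Expected change from baseline:

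| Study 1 | Follow-up 1 | Follow-up 2 |
|---|---|---|
| First start (3 schools) | t1 + d0 | t2 + d1 |
| Second start (3 schools) | t1 | t2 + d0 |

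| Study 2 | Follow-up 1 | Follow-up 2 | Follow-up 3 |
|---|---|---|---|
| First start (2 schools) | t1 + d0 | t2 + d1 | t3 + d2 |
| Second start (2 schools) | t1 | t2 + d0 | t3 + d1 |
| Third start (2 schools) | t1 | t2 | t3 + d0 |

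**Isolated regression.** (t2 + d1) − (t1 + d0) = (d1 − d0) + (t2 − t1). The bias is t2 − t1, the drift over one term.

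**Concurrent comparisons at follow-up 2.**
- Both studies, first-start minus just-finished schools: (t2 + d1) − (t2 + d0) = d1 − d0. The period effect cancels. This needs d0 to be the same in both terms of delivery.
- Study 2, first-start minus still-waiting schools: (t2 + d1) − t2 = d1. This is the controlled effect one term after the programme; it is not in itself a test of fading.

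A model with an intercept, assessment effects and time since programme has 1 + 2 + 2 = 5 columns in Study 1 and 1 + 3 + 3 = 7 in Study 2. The design matrices have rank 5 and 7, so both models are identifiable.

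**Does the interaction fill the gap?** The text leaves open whether assessment is categorical or linear, so both were checked. The expressions below weight sequences equally.
- Categorical, Study 1: the rank is 4 with or without the interaction. Only follow-up 1 has both exposed and unexposed schools, so nothing is added.
- Categorical, Study 2: the rank rises from 5 to 6. The one extra contrast is (d1 + d0)/2 − d0 = (d1 − d0)/2, a diluted measure of fading.
- Linear, Study 1: exposed slope minus unexposed slope = [(t2 − t1) + (d1 − d0)/2] − t1. Period change drops out only if it is the same in each term.

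**Illustrative size.** Assumed: within-girl correlation 0.7, and drift as shown. From Power analysis: 10 girls per school. The variance of a girl's change is 2(1 − 0.7) = 0.6, so the standard error is √(0.6/30) = 0.14 SD with 3 schools and √(0.6/20) = 0.17 SD with 2. Simulated share of significant results with no true fading (two-sided 5%, girls as units):

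| Drift per term | 3 schools | 2 schools |
|---|---|---|
| 0 | 5% | 5% |
| 0.2 SD | 28% | 20% |
| 0.3 SD | 53% | 38% |
| 0.5 SD | 92% | 79% |

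In the other direction, true fading of 0.3 SD with an upward drift of 0.3 SD gives −0.3 + 0.3 = 0.00 in isolation, significant in about 5% of runs. The concurrent contrast recovers −0.30.

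**Precision of the concurrent contrast.** Its standard error is √(2 × 0.6/30) = 0.20 SD with 3 schools per sequence and √(2 × 0.6/20) = 0.245 SD with 2. With school-level degrees of freedom of 4 and 2, the 95% half-widths are 2.776 × 0.20 = 0.56 SD and 4.303 × 0.245 = 1.05 SD, before any school-by-term variation is added.

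**The case against.** The strongest reply is that this is a supplementary look. The article gives a reading rule only for the interaction, and the hypothesis concerns improvement relative to the waiting list, not durability. That limits the weight of the point but does not remove it. Durability is a declared question, and in Study 1 the interaction cannot answer it cleanly, so the isolated regression would carry the answer.

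The second reply is that the controlled comparison is weak. With half-widths of about 0.56 and 1.05 SD it could reveal a near-complete loss of the 1.5 SD effect assumed under Power analysis, but not a change of 0.2 to 0.3 SD. It also needs the immediate effect to be equal across terms, which Study 1 cannot verify. This stands. It is why the isolated regression is better kept as description than deleted.

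Several stronger readings are not supported:
- A reader might infer that the plan ignores its comparator altogether. It does not. The main mixed model uses all schools and codes waiting schools as unexposed; only this regression leaves them out.
- A reader might blame regression to the mean, since girls are referred for low self-esteem and similar problems. Selection precedes baseline, so most of that shift should occur before the first post-programme assessment, where this contrast begins.
- A reader might take the pilot remark as rejecting every uncontrolled comparison. It concerns establishing efficacy and does not address a supplementary follow-up within a randomised trial.
- A reader might treat clustering by student only as a second proven error. Stable school differences cancel in within-girl change. Only school-by-term shocks matter, and the article gives no size for them. Assumed shocks of 0.15 to 0.25 SD raise the 5% error rate to about 9% to 15%.

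**Conclusion.** The point holds in a limited form. The isolated regression estimates fading plus period change and cannot tell them apart. That follows from the design and needs no numerical assumption. The bias equals the drift per term, and the article gives no figure for it. The rejection rates are illustrations under an assumed correlation and assumed drifts, not estimates of this trial's error rate; with no drift and no school-by-term shock the rate is the nominal 5%. The estimate of the main programme effect is untouched. The conclusion at risk is whether the benefit lasts, chiefly in Study 1, where the interaction offers no clean substitute.

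**What to change.** Rewrite the sentence so that the sustained-effect conclusion rests on the randomised sequences:
- Fit a model with fixed assessment effects, time since programme (just finished, one term past and, in Study 2, two terms past) and random school and student effects.
- State the assumption that the immediate effect does not depend on the term of delivery.
- In Study 2, also report first-start against still-waiting schools at follow-up 2, described as the controlled effect one term after the programme.
- Keep the isolated regression as a descriptive, uncontrolled summary. Say that Study 2 has no unexposed schools at its last assessment, so persistence at that point has no untreated comparator.

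This takes a short change to the analysis text and no new data. The cost is a wide interval from 2 or 3 schools per sequence, which should be reported as such; a non-significant difference should not be read as proof that the effect was sustained.

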### Participants and setting

Participants in this study were either high school or primary school students who were referred to the Greater Dandenong Community Health Centre to receive the intervention program. The intervention was a program being run prior to the conduct of this trial and schools in the City of Greater Dandenong municipality had been routinely referring students to this program for the previous 8 years. Each school group consisted of between 8–12 participants.

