### Power analysis

Analysis of data from the pilot study indicated that the effect of the “Girls on the Go!” program on participant self-esteem was very strong (ie. Change in outcome is 1.5 times the width of the standard deviation). Assuming 80% power, only 10 participants per group will be required in a standard randomised trial with randomisation of individual participants. This study will be a cluster randomised trial however to account for a variance inflation factor (design effect) of 3 (where average size per cluster is n =10, and the ICC is assumed to equal 0.33) then a total of 120 participants in both the primary (n = 60) and secondary (n = 60) schools will be required.

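### The supplementary first-versus-later check of sustained effect uses student-clustered linear regression, which, unlike the planned mixed model, is biased if loss depends on the first post-programme score (minor)

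*Protocol article*

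**What the plan says.** All of this is in the Analyses section of the protocol article.

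- **Main model.** A linear mixed model is chosen as "suitable for analysing longitudinal data where there is likelihood of missing data or loss to follow-up". On estimation the section says: "Maximum likelihood methods of estimation will be employed to address issues of missing data under the assumption of Missing At Random".
- **Sustained effect, first test.** An interaction of programme "by assessment interaction effect will be added to the same analysis models", so this test stays within the maximum-likelihood framework.
- **Sustained effect, second test.** The next step opens "We will also examine the data from the group that received the" and takes only the schools treated first. The aim is to "compare student results between the first and subsequent post-intervention follow-up assessments in isolation using linear regression clustering data by individual student". No missing-data rule is given for this step.

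The section on the pilot shows what the authors mean by clustering. There it is "clustering by participant to account for dependency between pre and post assessments within participant", that is, an allowance for correlated observations and not a treatment of missing ones.

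**The concern.** The plan expects girls to be lost and picks an estimator for that reason. For one contrast it then names a different estimator without that property. A student-clustered linear regression of score on assessment has the same coefficient as ordinary least squares. If all available surveys are used, that coefficient is the mean of the girls surveyed later minus the mean of all girls surveyed first. A girl who gives only the first post-programme survey counts in one mean and not in the other.

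If those girls differ in score from the girls who stay, part of the estimated change reflects who remained. The contrast is meant to show whether gains last, so such bias could make fading look smaller or larger than it is. A method that avoids this under the plan's own missing-at-random assumption is already specified a few lines earlier.

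**Working it through.** The article gives no figure for this contrast; its power calculation concerns the programme effect only. There is therefore nothing to reproduce, and the size has to be shown under stated assumptions.

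**Inputs from the article**
- School groups: "Each school group consisted of between 8–12 participants". The first-treated group is 3 schools in Study 1 (3 × 8 to 3 × 12 = 24–36 girls) and 2 schools in Study 2 (16–24 girls). I use 30 girls, that is, 3 × 10.
- Loss to follow-up is expected, but no rate is stated.

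**Assumptions (not in the article)**
- Post-programme scores have SD 1, with higher meaning better. The correlation ρ between first and later score is 0.5 or 0.7.
- Loss after the first post-programme survey follows a logistic model on that first score, so it is missing at random. Low scorers are more likely to be lost, with an odds ratio of 2.7 or 1.65 per SD.

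**Formulas.** Let Y1 have mean 0, let Y2 = δ + ρY1 + error, and let k be the mean of Y1 among girls who stay.
- Unpaired regression: E(Y2 | stay) − E(Y1) = δ + ρk. Bias = ρk.
- Completers only (paired): E(Y2 − Y1 | stay) = δ + ρk − k. Bias = −(1 − ρ)k.
- Likelihood: regresses Y2 on Y1 among those who stay and evaluates at the mean of all girls' Y1, which gives δ. Bias = 0.

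**No true change (δ = 0).** Here k comes from numerical integration of the logistic loss model.

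| Odds ratio per SD | Lost | k | ρ | Unpaired ρk | Paired −(1 − ρ)k | Likelihood |
|---|---|---|---|---|---|---|
| 2.7 | 22% | 0.189 | 0.5 | 0.095 | −0.095 | 0.00 |
| 2.7 | 22% | 0.189 | 0.7 | 0.132 | −0.057 | 0.00 |
| 2.7 | 16% | 0.141 | 0.5 | 0.070 | −0.070 | 0.00 |
| 2.7 | 16% | 0.141 | 0.7 | 0.099 | −0.042 | 0.00 |
| 1.65 | 19% | 0.092 | 0.5 | 0.046 | −0.046 | 0.00 |
| 1.65 | 19% | 0.092 | 0.7 | 0.064 | −0.027 | 0.00 |

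Simulation with 30 girls and 4,000 replicates per row agrees: 0.05 to 0.13 SD for the unpaired regression, and within 0.004 of zero for likelihood.

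**True fading of 0.30 SD, 20% lost, steeper dependence (log odds 1.5 per SD, k = 0.227)**
- Unpaired: −0.30 + 0.5 × 0.227 = −0.19, or −0.30 + 0.7 × 0.227 = −0.14.
- Paired: −0.30 − 0.5 × 0.227 = −0.41, or −0.30 − 0.3 × 0.227 = −0.37.
- Likelihood: −0.30 in both.

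**Other patterns of loss (same 20%, true change −0.30)**
- Loss unrelated to scores: all three give −0.30.
- Loss of high scorers: the unpaired estimate moves the other way, to −0.41 or −0.46. Likelihood stays at −0.30.
- Loss of girls whose unseen later score is low (not missing at random): unpaired −0.07, likelihood −0.12 (ρ = 0.5) or −0.17 (ρ = 0.7). Both are biased, likelihood less so.

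**Against sampling error.** With 30 girls the student-clustered standard error is 0.17 to 0.21 SD. At a nominal 5% level with no true change, the regression rejects in about 5 to 7% of replicates in five of the six settings, and in about 9% in the worst (ρ = 0.7, 22% lost).

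**The case against.** The strongest case on the other side has four parts.

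- **The check is supplementary.** The interaction in the mixed models comes first and the regression is an addition. This stands. A reader might infer that any claim of sustained effect would merely reflect retention. The article does not support that, because the claim does not rest on this regression alone. How well the interaction answers the question is a separate matter, not relied on here.
- **A simpler check beside a likelihood model is not a contradiction, and the text does not say whether girls with one survey are kept.** This stands in part. The unpaired reading is the plain one, but a completers-only reading is possible. It does not rescue the method: under the same loss it is biased in the opposite direction, by about −0.03 to −0.09 SD with no true change.
- **The size is assumed and is below the noise.** This stands. Neither loss rate nor correlation is in the article, and the bias is smaller than one standard error. It is also under a tenth of the programme effect assumed in the power analysis ("Change in outcome is 1.5 times the width of the standard deviation"; 0.13 / 1.5 = 0.09), although that is an effect of the programme and not a yardstick for fading.
- **Schools.** A reader might add that ignoring school makes the standard error too small, since only 2 or 3 schools are involved. That is not supported. First versus later is a contrast within girl and within school, so a constant school effect largely cancels. In a simulation of 3 schools of 10 with school ICC 0.33 and 20% random loss, adding a school intercept left the standard error at 0.163.

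**Conclusion.** The point holds as a minor one. For a supplementary contrast the plan names an estimator that needs loss to be unrelated to scores, while the same section expects loss and already specifies a method valid under missing at random. Under the assumed loss of 16–22% that depends on the first post-programme score, the regression is off by about 0.05 to 0.13 SD and likelihood by 0.00.

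The direction is not fixed, so the documents do not support saying that the check will hide fading; it can hide or exaggerate it, depending on who is lost. Nor does the point reach the primary effect estimate, which comes from the mixed model. The size depends entirely on assumed loss and correlation.

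**What to change.** Replace the linear regression for this contrast with the maximum-likelihood mixed model already planned. Restrict it to post-programme assessments in the first-treated group, with time since programme as a fixed effect and a random intercept for student. Keep every girl who has a first post-programme survey, and report how many girls have only one survey. Any paired comparison of girls with both surveys should be labelled descriptive only.

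The cost is a change of wording and no new data. The downsides are slightly more modelling for a supplementary check, and a result that still rests on missing at random: if girls leave because they have faded, the mixed model is biased too, though less than the regression.

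### The isolated first-versus-later comparison clusters by student only, so its standard error is too small if girls in the same school change together after the programme

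*Protocol article*

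**What the plan says.** The Analyses section of the protocol article gives two ways to judge whether an effect lasts. The first adds a programme-by-assessment interaction to the mixed model. The second takes only the group treated first and will "compare student results between the first and subsequent post-intervention follow-up assessments", and this is to be done "in isolation using linear regression clustering data by individual student". No school term and no clustering by school is named for the second analysis.

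Elsewhere the article treats school as a level that matters:

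- The Design section describes a programme "delivered to a group of participants from the same school at the same time". It gives this as the reason for allocating whole schools and not individual girls: "randomising students in clusters (school) was seen as an appropriate unit of randomisation".
- For the main model, the Analyses section states: "Assessment will be nested within student which will be nested within school which will create a 3-level model".
- The Power analysis section inflates the sample size for clustering, "where average size per cluster is n =10, and the ICC is assumed to equal 0.33".

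The first-treated group has 3 schools in Study 1 and 2 schools in Study 2.

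**The concern.** Clustering by student deals with the repeated surveys of the same girl. It then treats the roughly 20 to 30 girls as independent of one another. They come from only two or three schools, and each school's girls went through the programme as one group. If girls in one school drift up or down together after the programme, for instance through their continuing peer group or events at that school, each girl adds less independent information than the regression assumes.

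The confidence interval would then be too narrow, and movement peculiar to two or three schools could be reported as a general fading or further gain. What is at stake is the statement about durability, not the estimate of the programme's effect against the waiting list.

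**Working it through.** **Plan's own figure.** The article states no precision, power or ICC for this comparison, so there is nothing to reproduce. The ICC of 0.33 and cluster size of 10 in the Power analysis section serve to size the trial. The article does not say that 0.33 applies to change between two post-programme surveys.

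**Inputs from the article.** Schools in the first-treated group: K = 3 (Study 1) and K = 2 (Study 2). Girls per school: m = 10. Post-programme assessments in this group: 2 in Study 1 and 3 in Study 2, which has one further follow-up.

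**Assumptions.** Two-sided 5% test, complete data, no true average change, and an ICC of the within-girl change, ρ, of 0 to 0.10.

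**Step 1: what cancels.** Write a girl's change (later minus first) as d = μ + b + w, where b is the part shared by her school and w is her own part. A constant school effect is present in both scores and drops out of d. Only the variance of b matters, with ρ = Var(b) / [Var(b) + Var(w)].

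**Step 2: size of the error.** The variance of the mean change is σ²[1 + (m − 1)ρ] / (Km). The student-clustered standard error estimates approximately σ² / (Km). The ratio of true to reported standard error is therefore about √[1 + (m − 1)ρ]:

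- ρ = 0.02: √(1 + 9 × 0.02) = √1.18 = 1.09
- ρ = 0.05: √(1 + 9 × 0.05) = √1.45 = 1.20
- ρ = 0.10: √(1 + 9 × 0.10) = √1.90 = 1.38

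**Step 3: false-positive rate.** Simulation of the named method (least squares on a first/later indicator with student-clustered standard errors), 20,000 trials per cell, with a school ICC of 0.33 in the scores:

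| ICC of change | Study 1 (3 schools) | Study 2 (2 schools) | True / reported SE |
|---|---|---|---|
| 0 | 4.9% | 4.9% | 0.99 |
| 0.02 | 6.8% | 6.8% | 1.08 |
| 0.05 | 10.0% | 10.0% | 1.20–1.21 |
| 0.10 | 15.5% | 15.3% | 1.40 |

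With a score ICC of 0 instead of 0.33, the rates are almost the same (4.8% to 15.5% in Study 1, 5.0% to 15.0% in Study 2). The score ICC therefore plays no part. A second simulation, using a one-sample t-test on complete pairs with 40,000 trials per setting, gave 5.0%, 7.0%, 10.7% and 15.7% with 3 schools and 5.0%, 7.1%, 10.4% and 15.6% with 2 schools.

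**Step 4: what a school-level test would leave.** A t-test on the school mean changes holds its level (4.7% to 5.2% in every setting tried). It has 3 − 1 = 2 or 2 − 1 = 1 degrees of freedom, with critical t values of 4.30 and 12.71. The student-level analysis behaves as though it had 30 − 1 = 29 or 20 − 1 = 19.

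**Step 5: would the main model's structure help?** A school random intercept is a constant school effect, so it cancels in this contrast just as in Step 1. A rough check with 250 runs per cell and many convergence warnings, so indicative only, compared a paired test with a student-plus-school random-intercept model at ρ = 0.10. Rejection was 15% and 19% with 3 schools, and 14% and 18% with 2 schools. The intercept gave no protection.

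**The case against.** The strongest reply is that inflation is possible but not shown. With no shared change, the named method holds its 5% level even when the scores have a school ICC of 0.33. A simulation that puts in shared change can only return its consequence. Some sources of shared change are also limited: both surveys follow the programme, and the Procedure section has one investigator administering them. Finally, the Analyses section attaches its rule about significance to the interaction test; the isolated comparison is an addition with no stated threshold.

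Most of this stands, and it sets the strength of the point. Two stronger readings should be avoided:

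- A reader might carry the 0.33 over to change and conclude that about a third of null comparisons would be declared significant (the simulations give 33% to 35% at that value). The article gives no basis for applying 0.33 to change.
- A reader might infer that the main model handles school correctly and that this regression merely departs from it. Step 5 shows otherwise: no school-by-assessment term is described for the main model, and its school intercept would not repair this contrast.

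What the reply does not remove is that the method is valid only if shared change is nil. The programme description makes that hard to take for granted. It reports close bonds within each group and content adapted to the group's needs, and Table 1 (Session 10) prepares girls to run activities in their own school afterwards. An unseen analysis plan does not settle the matter either, since the article itself names the clustering level.

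**Conclusion.** The point holds conditionally and is minor. The named regression gives a standard error that is too small if girls of the same school change together between post-programme surveys. This is plausible for a programme given to one intact group per school, but the article neither quantifies nor excludes it. If the ICC of change is zero, there is no inflation. At assumed values of 0.02, 0.05 and 0.10, the false-positive rate is about 7%, 10% and 15%, and the true standard error is about 1.1, 1.2 and 1.4 times the reported one. These figures rest on 10 girls per school and complete data. With 3 or 2 schools, the data cannot support a dependable test of this contrast under either form of clustering.

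**What to change.** In the Analyses section, replace the student-clustered regression test with wording such as:

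> For the schools that received the programme first, the mean change from the first to each later post-programme assessment will be reported separately for each school. This is descriptive: no p-value will be given, and no conclusion that an effect was sustained or lost will be drawn from this subset.

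Optionally, add a random school-by-assessment term with a small-sample degrees-of-freedom correction to the full-sample mixed model, labelled as a sensitivity analysis. With six schools per study, and only three in Study 1 having more than one post-programme assessment, that variance will be imprecisely estimated, and the plan should say so.

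The cost is a wording change and the loss of one p-value for a supplementary comparison. No new data are needed.
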